**Study design**

*CONFIDENTIAL*

*Division of Prevention and Community Health, National Center for Cardiovascular Disease, China*

The study is a two-phase design. First, a cross-sectional survey designed to evaluate the prevalence and management of hypertension among Chinese working population. Then, a cluster-controlled trial conducted to test the effect of a multicomponent intervention strategy on improving hypertension control in workplaces.

For this program, a coordinating center will be established at Fuwai Hospital, Beijing. Then, 20 urban medical institutions will be selected as sub-centers, representing various geographic locations in China. Subsequently, 2 to 4 workplaces will be recruited by each sub-center, to test the feasibility of the protocol in work settings, all of which should meet the following criteria: (1) more than 50 patients can be recruited per site; (2) workplaces within the same sub-center should be matched by sector, ownership, size, economic level and medical condition; (3) none similar programs were conducted before; (4) non-medical institutions; (5) agrees to participate in the program for a minimum of 2 years; (6) agrees to arrange at least one full-time or part-time project officer to execute the workplace wellness program; and (7) can select a designated hospital clinic for implementing the standardized HTN management for 2 years.

Within each sub-center, 1 to 3 workplaces will be assigned to the intervention group, and one workplace assigned to the control group, with approval from manager of each workplace. To minimize the potential imbalance between groups, workplaces assigned to the intervention and control group within each sub-center, should be matched by sector, ownership, size, economic level and medical condition. Within each sub-center, at least 50 potential participants will be selected and invited for

89 baseline assessments at each workplace, and the patients will be allocated to  
90 intervention or usual care in a 3:1 ratio.

91 For the intervention patients alone, there will be monthly follow-up visits within  
92 the 2 years duration by their physicians. Patients in the control group carry on with  
93 their usual health care.

94

95 **Study Duration:**

96 Subjects will receive intervention for a minimum of 24 months.

97

98 **Study Inclusion and Exclusion Criteria:**

99 **Inclusion Criteria:**

- 100 1. Subject has a clinical diagnosis of HTN;
- 101 2. Subject is aged 18 to 60 years;

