- 102 3. Subject is under a fixed term employment contract;
- 103 4. Subject has provided signed consent form;
- 104 5. Subject agrees to participate in the study for the full 2 years duration.

105 **Exclusion criteria**

- 106 1. Subject has secondary hypertension;
- 107 2. Subject has acute myocardial infarction or stroke less than 3 months;
- 108 3. Women who self-reports being pregnant or within 3 months postpartum;
- 109 4. Subject with life expectancy of less than 2 years;
- 110 5. Subject with psychiatric illness, hearing difficulty, or physical incapacitation;

6. Subject is a healthcare provider.

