### **Sample Size Considerations:**

The study is designed as an effectiveness trial of active interventions, compared with the usual care group. On the basis of previous literature, we expected that 20% of patients in the control group would be properly controlled, whereas we expected patients in the intervention group to increase this to 50% control at 24-month follow-up. Considering the intervention benefits and ethical issues, the study was designed to recruit patients using a 3:1 ratio. Cluster randomization power analysis was performed for the two independent proportions, and with a 2.5% type I error and intra-cluster correlation coefficient (ICC) of 0.01, we estimated that a sample size of 3,000 intervention patients (cluster size 75) and 1,000 control patients (cluster size 50) would provide 90% power to detect an improvement of 25% in BP control between the two groups and allowing 20% loss to follow-up in each group. To ensure an enough power, 3,600 intervention patients and 1,200 control patients were recruited in this study.

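### Workplaces appear to be assigned before patients are selected, with no common selection rule and no concealment of the arm, so selection and consent can make the arms differ

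*Protocol*

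**What the plan says.** The Protocol, Study design, plans "a cluster-controlled trial conducted to test the effect of a multicomponent intervention strategy". It states that "20 urban medical institutions will be selected as sub-centers", each recruiting 2 to 4 workplaces. On assignment it says: "1 to 3 workplaces will be assigned to the intervention group, and one workplace assigned to the control group, with approval from manager of each", meaning each workplace. Workplaces in the two arms "should be matched by sector, ownership, size, economic level and medical condition".

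Patients come next in the text: "Within each sub-center, at least 50 potential participants will be selected and invited for" a first examination. The same sentence ends with "baseline assessments at each workplace, and the patients will be allocated to", followed by the names of the two arms and the 3:1 ratio. No sampling method or upper limit is given, and nothing is said about who knows the arm at that time.

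Inclusion criterion 5 reads "Subject agrees to participate in the study for the full 2 years duration". Monthly visits are planned for intervention patients only; both arms are examined at baseline and at 24 months (Study design; Effectiveness assessments).

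Sample Size Considerations plans "3,000 intervention patients (cluster size 75) and 1,000 control patients (cluster size 50" in the control arm), then raises the recruitment target to 3,600 and 1,200. Statistical Methods compares the arms at baseline, contrasts change from baseline, and adjusts for baseline covariates.

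**The concern.** In a cluster trial, patients enrolled after the workplace's arm is known are exposed to a second selection step that assignment does not protect. A project officer or clinic that knows the arm may approach different employees, and employees who know it may accept or decline for different reasons. Here the commitment in criterion 5 means about 24 clinic visits (12 × 2) in one arm and two examinations in the other. Willingness to accept that burden is plausibly related to later blood pressure control.

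Matching workplaces does not help with this, because the difference arises among patients within a workplace. At stake is whether the 24-month contrast in control rates reflects the programme alone or partly who was enrolled.

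**Working it through.** **Step 1: order of the steps.** Three statements in Study design, side by side:

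- Workplaces are assigned, with manager approval. The arm is then known to at least one person on site.
- Patients are selected and invited for baseline assessment at each workplace.
- Patients are allocated 3:1.

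The first and second suggest assignment before selection. The third, read alone, suggests allocation of patients after baseline. Patient-level allocation fits poorly with the Workplace component section, which delivers the wellness programme to the whole workforce of a site. The assignment reading is therefore the more coherent one, but no timeline settles it.

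**Step 2: planning figures for cluster size** (Sample Size Considerations).

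- Intervention workplaces: 3,000 / 75 = 40.
- Control workplaces: 1,000 / 50 = 20, which fits 20 sub-centers with one control workplace each.
- Workplaces are 40:20 = 2:1 and patients 3,000:1,000 = 3:1, so patients per workplace differ by 75 / 50 = 1.5.
- At the raised target with the same workplaces: 3,600 / 40 = 90 against 1,200 / 20 = 60, again 1.5.

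**Step 3: is the unequal size needed?** Study design allows up to three intervention workplaces per sub-center.

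- 20 × 3 = 60 intervention workplaces × 60 patients = 3,600.
- 20 × 1 = 20 control workplaces × 60 patients = 1,200.

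The target and the 3:1 ratio are both met with equal cluster sizes. Power gives no reason against it. With ICC 0.01, 20% loss, a control rate of 20% and two-sided alpha 0.025, power for 25 points exceeds 99.9% either way. The difference detectable with 90% power is 6.8 points with 60 per workplace in both arms and 6.9 points with 90 against 60.

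**Step 4: what a selection shift would do, if there were one.** The documents give no value for the shift, so it is assumed, over a range. The control rate is 20% in both arms, there is no true effect, and there is no baseline adjustment.

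- After 20% loss: 2,400 patients in clusters of 60 and 800 in clusters of 40.
- Design effect 1 + (m − 1) × ICC: 1 + 59 × 0.01 = 1.59 and 1 + 39 × 0.01 = 1.39.
- Effective sizes: 2,400 / 1.59 = 1,509 and 800 / 1.39 = 576.
- For a 5-point shift (25% against 20%), the pooled rate is 0.236. The SE is 2.08 points under the null and 2.01 points under the shift.
- Probability of significance at two-sided 0.05: Φ((5 − 1.96 × 2.08) / 2.01) = Φ(0.46) = 68%.

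| Assumed shift (points) | Two-sided 0.05 | Two-sided 0.025 |
|---|---|---|
| 2 | 16% | 10% |
| 3 | 31% | 22% |
| 5 | 68% | 57% |
| 10 | 99.7% | 99% |

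The 0.05 level is that of Statistical Methods; 2.5% is the type I error in Sample Size Considerations, where sidedness is not stated. The figures depend on the ICC: at ICC 0.05, the 57% falls to 26%.

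**The case against.** Several points count against a strong version of this concern, and most of them stand.

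- The order is inferred from the sequence of the text and from manager approval. The sentence on 3:1 allocation can be read the other way. This stands as a limit, but it also shows that the section must be reconciled.
- A reader might infer from 75 and 50 that recruitment quotas differ by arm, so that selectors must know the arm and must take a larger share of hypertensive staff in intervention workplaces. The documents do not support this. The two figures are sample-size inputs, the only recruitment rule is the same minimum of 50 in both arms, and Step 3 shows that equal sizes are possible. Matching on size also does not establish equal numbers of hypertensive employees. Unequal cluster sizes do not bias a random sample.
- A reader might also infer that intervention patients are in effect pre-screened for motivation, so the effect is inflated. This is not shown either. Criterion 5 is worded identically for both arms, and the consent form is not at hand to show what patients are told. The mechanisms can also oppose each other: recruiting a larger share of eligible staff would, if anything, select less for motivation.
- The analysis contrasts change from baseline and adjusts for baseline covariates. This helps with measured factors. Appendix B has no item on motivation or willingness to attend, and subtracting baseline does not cancel a difference in expected improvement or in regression to the mean. The mitigation is therefore partial.

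**Conclusion.** The concern holds as a risk, not as a demonstrated bias. As written, Study design describes assignment before selection, gives no common selection rule, and provides no concealment, while the burden accepted at consent differs by arm. Enrolled patients can then differ between arms in unmeasured ways that the planned adjustment does not remove.

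Size and direction cannot be derived from the documents, and the table above only shows sensitivity to assumed shifts. A shift of 2 to 5 points would not overturn a planned difference of 25 points, but it would distort the estimate and would matter more if the true effect were small. The ratio of 1.5 in patients per workplace follows from the planning figures; it is not a defect in itself and is not evidence of arm-specific quotas.

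The conclusion rests on reading the order of the text as the order of events. If the intended order is different, the section still needs to say so.

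**What to change.** In Study design:

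- State one sequence and one unit of assignment, and reconcile the sentence on allocating patients 3:1 with the assignment of workplaces.
- Use the same selection rule in every workplace of a sub-center: all eligible hypertensive employees, or a random sample of them.
- Complete consent and the Appendix B baseline visit before the arm is disclosed to the project officer, the clinic and the patients. Agreement to two years then carries the same meaning in both arms.
- Where possible, reach 3:1 through the number of intervention workplaces rather than through larger samples per workplace.

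Cost: mainly a reordering of existing steps, with a short delay in disclosing the arm. Managers' approval would have to cover either arm or be kept from those who select patients. Each workplace needs a list of hypertensive employees; the phase-1 survey may supply it, but the Protocol does not say that it covers the trial workplaces. The layout of 60 and 20 workplaces needs all 20 sub-centers to recruit their maximum of four. With only 40 intervention workplaces and equal samples, the patient ratio would be 2:1. That leaves power for 25 points above 99.9% under the planning assumptions, but it gives up the 3:1 ratio that Sample Size Considerations justifies by intervention benefit and ethics.

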## **Intervention Strategy**

The intervention will last for 2 years, and include two components: (1) workplace wellness program for primary prevention of CVD, the development of comprehensive health promotion within workplace to increase individual employees' awareness of risk factors and produce sustained behavior change, and (2) a standardized protocol of HTN management, the implementation of guideline-based HTN management by patients' clinical teams to improve HTN control.

### **1. Workplace component**

A comprehensive, culturally sensitive workplace wellness program aiming at improving employees' cardiovascular health will be implemented, in reference to the recommendations from AHA, and Chinese Guidelines for the Management of Hypertension. The program should better be integrated into the organizational structure of the workplace, and new initiatives should rely on existing valid sources. The project officers will be responsible for coordinating all events within workplaces. It should be noted that the program will be delivered to the whole workforce population, despite only certain number of hypertensive patients will be selected for assessments on each site. Specifically, the workplace wellness program includes the following components: (1) CVD health education. The project officers should organize lectures, put up posters and/or send text messages to educate employees

about the knowledge of risk or prevention of CVD. The topics including prevalence, risk factors and management of CVD, and strategies for behavioral changes, etc. (2) Reasonable diet. Nutrition education and/or healthy diets information were provided to the employees. In addition to the previously-served food, easy access, affordable, healthy foods (e.g., low-salt, low-fat food) were offered in the cafeteria, and the participants were encouraged to select it to eat from the menu when they have lunch in the cafeteria in their worksites. (3) Tobacco cessation. Tobacco control regulation was developed to improve tobacco cessation among the employees, and no smoking was permitted in the workplaces. (4) Environment promotion. The improvements of physical environment include modifying workstations and office layouts to decrease sedentary behavior, encouraging physical activity. (5) Physical activity. Participants were encouraged to increasing physical activity within exercise breaks during working hours. Accessible indoor or outdoor sports facilities were provided to engage employees in regular physical activity, including an indoor walking path. (6) Stress management. Relaxation techniques were provided by the employees specialized in meditation, tai-chi or deep breathing for dealing with stress monthly. (7) Health screening. Health checkup were offered annually, and feedback was provided to identify the key risk factors.

## **2. Clinic component**

Employees with hypertension will be managed for at least 2 years by physicians in the clinics trained by a standardized BP management protocol. The protocol, which is based on Chinese Guidelines for the Management of Hypertension, include the

following: classification of HTN, stratification of global risk, targets for BP control, the principles of treatment, lifestyle changes, drug treatment, and follow-up management. BP control targets are as follows: <140/90 mmHg for uncomplicated hypertension; <130/80 mmHg for patients with diabetes, cerebrovascular disease, stable coronary heart disease, or chronic renal failure. The principles of treatment is based on patients' risk stratification. The physicians should make oral health education on lifestyle changes and prescribe the drugs according to patients' conditions. The patients will be instructed to visit the designated clinics monthly until the end of this trial, during which the measurement of BP as well as the adjustment of individual therapeutic regimen made. The project officers should be responsible for supervising and assisting hypertensive patients in regular follow-up. Moreover, patients will be referred to a higher-level hospital when necessary, and then return to the designated clinics for follow-up when they are in a stable condition.

### **Effectiveness assessments**

There will be two examinations for both groups, at baseline and 24 months (after 2 years intervention). Indicators including BP, BMI and lifestyle factors will be assessed.

All outcome assessments will be conducted at baseline and at 24-month follow-up in exactly the same way in the clinics for all patients, irrespective of their assignment to intervention or control group. For the intervention patients, monthly follow-up visits will be made within the 2 years duration to document the BP and lifestyle factors.

177

178 **Statistical Methods:**

179 All patients who attended follow-up visits at 24 months and had complete data for the  
180 primary outcome and other variables were included in the analysis. The baseline  
181 differences between patients included and unincluded, patients in the intervention  
182 group and those in the control group, will be examined by mixed-effects model. All  
183 patients who attend follow-up visits at 24 months and have complete data for the  
184 primary outcome may be included in the analysis, without imputation for missing data.  
185 The intervention effect will be performed as the difference between two groups, it will  
186 be calculated as intervention (values at 24 months minus values at baseline) minus  
187 control (values at 24 months minus values at baseline), and evaluated by  
188 mixed-effects models (PROC MIXED for continuous variables, PROC GLIMMIX for  
189 categorical variables), which included a random cluster effect (workplace). Group  
190 (intervention, control), all the baseline covariates, and potential interaction terms were  
191 used for adjustment in all models. The subgroup analyses of primary outcome will be  
192 conducted to assess the intervention effect on subgroups of education, occupation  
193 status, workplace ownership, and workplace-affiliated hospital. To evaluate the  
194 robustness of the results of the primary analyses, multiple-imputation method was  
195 adopted to handle missing data on outcome and covariates in a sensitivity analysis.  
196 The results will be summarized as rate (%), mean, standard deviation (SD), standard  
197 error (SE), and 95% confidence interval (CI) when appropriate. All data analyses will  
198 be conducted using SAS 9.4 (SAS institute, Cary, NC, USA) and a two-sided *P*-value

<0.05 will be considered statistically significant.

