**Secondary Objective(s):**

- Assess the changes of BP level from baseline to the 24-month follow-up.
- Assess the changes in prevalence of smoking, drinking, exercise, and overweight/obese, from baseline to the 24-month follow-up.

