- 334 Section D: Lifestyle factors
- 335 D1. Do you prefer eating salty food regularly?      ①No   ②Yes
- 336 D2. Do you perceive high levels of stress recently?   ①No   ②Yes
- 337 D3. Do you smoke currently (at least one cigarette per day)? ①No   ②Yes
- 338      If yes, how many cigarettes do you smoke daily on average? \_\_\_\_\_
- 339 D4. Do you drink currently (consumption of at least 1 alcoholic beverage per week)?
- 340      ①No   ②Yes
- 341      If yes, how many times do you drink per week on average? \_\_\_\_\_
- 342 Section E: Physical examination and Biochemical test
- 343 E1. Height: \_\_\_\_\_ cm; Weight: \_\_\_\_\_ kg
- 344 E2. Blood pressure (SBP/DBP):
- 345      The first time \_\_\_\_/\_\_\_\_ mmHg; the second time \_\_\_\_/\_\_\_\_ mmHg;
- 346 E3: Fasting glucose: \_\_\_\_\_ mmol/L or \_\_\_\_\_ mg/dL
- 347 E4: Triglycerides: \_\_\_\_\_ mmol/L or \_\_\_\_\_ mg/dL
- 348 E5: Total cholesterol: \_\_\_\_\_ mmol/L or \_\_\_\_\_ mg/dL
- 349 E6: High density lipoprotein cholesterol: \_\_\_\_\_ mmol/L or \_\_\_\_\_ mg/dL
- 350

351      **Appendix C: Questionnaire (For monthly follow-up in intervention group)**

352      Sub-center ID \_\_\_\_\_      No. of work unit \_\_\_\_\_      No. of employee \_\_\_\_\_

353      Section A: Physical examination

*CONFIDENTIAL*

*Division of Prevention and Community Health, National Center for Cardiovascular Disease, China*

354 A1. Blood pressure (SBP/DBP):

355 The first time \_\_\_\_/\_\_\_\_ mmHg; the second time \_\_\_\_/\_\_\_\_ mmHg;

356 Section B: Lifestyle factors

357 B1. Do you prefer eating salty food regularly? ①No ②Yes

358 B2. Do you perceive high levels of stress recently? ①No ②Yes

359 B3. Do you smoke currently (at least one cigarette per day)? ①No ②Yes

360 If yes, how many cigarettes do you smoke daily on average? \_\_\_\_\_

361 B4. Do you drink currently (consumption of at least 1 alcoholic beverage per week)?

362 ①No ②Yes

363 If yes, how many times do you drink per week on average? \_\_\_\_\_

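### Smoking and drinking prevalence rest on unverified self-report, and only intervention patients answer the same items monthly at visits with counselling physicians, so one-sided under-reporting may pass for a lifestyle benefit

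*Protocol*

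**What the plan says.** Secondary Objective(s) includes: "Assess the changes in prevalence of smoking, drinking, exercise, and overweight/obese, from baseline to the 24-month follow-up". In Appendix B, the form for baseline and month 24, smoking is item D3, "Do you smoke currently (at least one cigarette per day", and drinking is item D4, "Do you drink currently (consumption of at least 1 alcoholic beverage per week". Both are answered no or yes. The laboratory fields in Section E cover glucose and lipids, so nothing on the form checks either answer.

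Appendix C is headed "Questionnaire (For monthly follow-up in intervention group", and its items B3 and B4 have the same wording as D3 and D4. Study design limits these contacts to one arm: "For the intervention patients alone, there will be monthly follow-up visits within" the two-year period, made by the patients' physicians. Effectiveness assessments gives their content: "For the intervention patients, monthly follow-up visits will be made within the 2 years duration to document the BP and lifestyle factors". The Clinic component says of the same physicians: "The physicians should make oral health education on lifestyle changes". Intervention workplaces also run health education and a tobacco-control programme (Workplace component), while controls continue usual care.

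The same Effectiveness assessments section has the outcome examinations done in the clinics by an identical procedure in both arms. Statistical Methods defines the effect as the change in the intervention arm minus the change in the control arm, tested at two-sided 0.05.

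**The concern.** An identical procedure makes the measurement comparable only if patients in both arms answer with the same candour. Here one arm reaches month 24 after up to 24 visits (monthly for 2 years) at which the same questions are recorded and lifestyle advice is given. The other arm has answered once before, at baseline. Some intervention patients may by then give the answer they know is wanted.

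The planned contrast removes under-reporting that is stable over time or equal in both arms. It does not remove extra under-reporting that arises after baseline in one arm only, and no later analysis can separate a denied cigarette from one no longer smoked. A significant fall in smoking or drinking could then be read as behaviour change when part or all of it is reporting. Only these two self-reported secondary outcomes are at stake; BP control, BP level and BMI are measured, not asked.

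**Working it through.** The Protocol gives no reporting-error figure, so there is nothing of its own to reproduce. The check has two parts.

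**1. Does the asymmetry exist in the text?**

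| | Intervention | Control |
|---|---|---|
| Smoking and drinking items at baseline and month 24 (Appendix B) | yes | yes |
| Same items monthly (Appendix C) | up to 24 times | never |
| Lifestyle education from the visit physicians | yes | usual care |
| Objective check of the answers | none described | none described |

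It does.

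**2. How much could it matter?** This is an illustration only.

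Inputs from the Protocol (Sample Size Considerations): 3,000 and 1,000 patients, clusters of 75 and 50, 20% loss, ICC 0.01.
- Analysed: 3,000 × 0.8 = 2,400 and 1,000 × 0.8 = 800.
- Cluster sizes after loss: 75 × 0.8 = 60 and 50 × 0.8 = 40.

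Assumed, not in the Protocol:
- true smoking prevalence p = 0.30 in both arms at both times (no real effect);
- within-patient correlation rho = 0.5 to 0.8;
- a share u of intervention smokers who newly deny smoking at month 24, with controls unchanged;
- an ICC for smoking of 0.01 or 0.05. The 0.01 is the Protocol's value for BP control, borrowed here.

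Bias in the difference of changes = −p × u. For u = 0.10: −0.30 × 0.10 = −3.0 percentage points.

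SE = sqrt{ 2p(1−p)(1−rho) × [DE₁/2,400 + DE₂/800] }, with DE = 1 + (m − 1) × ICC.

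- ICC 0.01: DE₁ = 1 + 59 × 0.01 = 1.59; DE₂ = 1 + 39 × 0.01 = 1.39; bracket = 0.0006625 + 0.0017375 = 0.00240.
  - rho 0.5: sqrt(0.21 × 0.00240) = 2.24 points.
  - rho 0.8: sqrt(0.084 × 0.00240) = 1.42 points.
- ICC 0.05: DE₁ = 3.95; DE₂ = 2.95; bracket = 0.001646 + 0.003688 = 0.00533.
  - rho 0.5: sqrt(0.21 × 0.00533) = 3.35 points.
  - rho 0.8: sqrt(0.084 × 0.00533) = 2.12 points.

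Probability of a significant result with no true effect = Φ(|bias|/SE − 1.96) + Φ(−|bias|/SE − 1.96). At u = 0.10, ICC 0.01, rho 0.8: 3.0/1.42 = 2.11, giving Φ(0.15) = 0.56.

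Results for p = 0.30 (range over rho 0.5 to 0.8):

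| Extra denial u | False fall, points | ICC 0.01 | ICC 0.05 |
|---|---|---|---|
| 2% | 0.6 | 6-7% | 5-6% |
| 5% | 1.5 | 10-18% | 7-11% |
| 10% | 3.0 | 27-56% | 15-29% |
| 20% | 6.0 | 76-99% | 43-81% |

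Prevalence matters too. At 10% extra denial and ICC 0.01 the range is 18-37% for p = 0.20 and 39-75% for p = 0.40. At 2% extra denial, everything from p = 0.20 to 0.40 stays within 5-8%. The same formulas apply to drinking with its own prevalence, which the Protocol does not give.

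**The case against.** The strongest reply is that the decisive link is not in the text. A reader might infer that at month 24 intervention patients give their outcome answers to the physician who has been counselling them. The Protocol does not say so. It places the examination in the clinics but does not say who administers Appendix B or whether patients fill it in themselves. Only the monthly visits are tied to the physicians. This stands, and it limits the point to a risk that the wording leaves open.

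The direction is not documented either. Patients whose physician already knows that they smoke might answer more consistently, not less. The workplace smoking ban adds little: D3 asks about current daily smoking, not smoking at work, so a truthful yes admits no breach. This also stands.

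The size depends on assumed values. A reader might take a false-positive rate of about a half as what the plan implies. The Protocol does not support that: it needs 10% extra denial, high within-patient correlation and an ICC borrowed from BP control. At ICC 0.05 the rate is about half as large or lower, and at 2% denial it is close to nominal.

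A reader might also infer that the monthly forms feed the outcome analysis. The headings of the two appendices and the two-examination schedule indicate that they do not, so no change is needed there.

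Finally, self-report bias is common in open behavioural trials, and these outcomes are secondary. That lowers the weight of the point. It does not answer it, because the repeated one-arm questioning is a specific feature of this design and the exposure can be reduced cheaply.

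**Conclusion.** The concern holds in a limited form. The text establishes unverified single-item self-report for smoking and drinking, and identical monthly questioning in one arm only, at visits with physicians who counsel on lifestyle. Neither the identical procedure nor the difference in changes protects against under-reporting that grows in one arm after baseline. Whether it occurs, in which direction and by how much cannot be learned from the Protocol.

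Under the assumptions above, it ranges from negligible (2% extra denial) to enough to make a spurious significant fall fairly likely (10% extra denial: 15-56% across the ICC and correlation values used). The larger recruitment figure of 3,600 and 1,200 would not dilute a bias of this kind. The primary outcome, BP level and BMI are untouched. This is a worthwhile low-cost improvement to data collection and a limit on interpretation, not a flaw in the main comparison.

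**What to change.** Add to Effectiveness assessments that, at baseline and at month 24 and in both arms, patients complete Section D of Appendix B themselves before seeing clinic staff or the project officer. The sheet carries an ID number rather than the name, is sealed and goes to the sub-center. It states that the patient's physician and employer will not see it. Report smoking and drinking as self-reported, and do not describe a significant fall as verified behaviour change.

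Sample Size Considerations describes recruitment in the past tense, so baseline may already have been collected. If it was collected in another way, do not change the mode at month 24 alone, because that would confuse a change of method with a change over time. Keep the same mode in both arms. Where possible, have existing staff other than the patient's treating physician or project officer take the month-24 Section D, and limit the conclusion to self-reported change.

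The cost is a procedure line and envelopes, with no extra staff or tests. Self-completion will leave somewhat more blank items, and the bias is reduced, not removed.
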